**Discussion:**

By comparing two traditional mind-body exercises against an active control group over 48 weeks, this trial is designed to determine whether these interventions offer durable clinical benefits as standalone therapies or provide additive value. The findings are expected to provide high-quality evidence regarding scalable, low-cost non-pharmacologic strategies for managing knee OA, with potential implications for public health policy.

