**Figure 1 F1:**
[figure not shown]
Study flow diagram.

The primary outcomes encompass the pain, stiffness, and physical function subscales of the Western Ontario and McMaster Universities Arthritis Index (WOMAC) (27). Secondary outcomes will be assessed using the Berg Balance Scale, which evaluates balance performance through a series of functional tasks; the 6-minute walk test, which measures endurance and mobility by assessing the distance walked in 6 min; and the Health Survey Short Form (SF-36), a comprehensive questionnaire that assesses overall health-related quality of life across multiple domains. These measures will provide a holistic view of the participants' physical and psychosocial well-being. Outcome measurements will be conducted at baseline, immediately following the 12-week intervention period, and at 24 and 48 weeks to assess the durability of treatment effects. The personnel administering the physical function evaluations and the data analyst are unaware of the participants' treatment allocations. The specific endpoints and their categorization as outcomes are detailed in Table 1.

**Table 1 T1:** Schedule of assessments for primary and secondary outcomes.

Time	Baseline	Week 12	Week 24	Week 48
Primary Outcome variables				
WOMAC^a^—Pain	×	×	×	×
WOMAC—Physical Function	×	×	×	×
WOMAC—Stiffness	×	×	×	×
Secondary outcome variables				
SF-36^b^	×	×	×	×
Berg Balance Scale^c^	×	×	×	×
6 min walk test^d^	×	×	×	×

a WOMAC: Western Ontario and McMaster Universities Osteoarthritis Index.

b SF-36: Medical outcome survey short-form 36.

c Berg Balance Scale: A 14-item test that measures a person's balance and walking abilities.

d 6 min walk test: A simple test that measures how far a person can walk in six minutes.

The study setting is the Zhongshan Hospital of Traditional Chinese Medicine, affiliated with Guangzhou University of Traditional Chinese Medicine, located in Zhongshan, Guangdong, China. The study received ethics approval from the Institutional Review Board of Zhongshan Hospital of Traditional Chinese Medicine.

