## Statistical analysis

All statistical analyses will be performed using SPSS Statistics version 26.0 (IBM Corp). Continuous variables will be first assessed for normality using the Shapiro–Wilk test and for homogeneity of variance using Levene's test. Data presenting a normal distribution will be expressed as mean ± standard deviation (SD). For comparisons among the three groups, one-way Analysis of Variance (ANOVA) will be used. If the ANOVA indicates a significant difference, *post-hoc* pairwise comparisons will be conducted using the Bonferroni correction to adjust for multiple testing. Non-normally distributed variables will be presented as median (interquartile range, IQR) and analyzed using the Kruskal–Wallis H test, followed by Dunn's test with Bonferroni correction for pairwise comparisons if significant. Categorical variables will be expressed as frequencies (percentages) and compared using the Chi-square test or Fisher's exact test where expected cell counts are less than 5.

For the primary outcome (change in clinical scores from baseline to post-intervention), repeated measures ANOVA will be employed, with Group as the between-subject factor and Time as the within-subject factor. If a significant interaction effect (Group × Time) is observed, simple main effects will be analyzed to determine differences between specific groups at each time point, with Bonferroni adjustments applied for multiple comparisons. A two-sided *p*-value < 0.05 will be considered statistically significant.

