### Analysis

The primary outcomes for this study are defined as the changes from baseline to Week 12 in the three WOMAC subscales: Pain, Stiffness, and Physical Function. The primary analysis will be conducted using an intention-to-treat approach, where all participants are analyzed in the group to which they were randomized, without adjustment for covariates, and with missing 12-week outcomes imputed as no change. Secondary analyses will adjust for baseline characteristics that differ significantly by treatment group, including gender, initial pain severity, medication use, disease duration, and the number of chronic conditions.

Changes in knee pain at weeks 24 and 48, along with all other outcomes, are considered secondary and will be analyzed in the same manner as the primary outcome. We will also perform a longitudinal analysis across all four time points to identify potential time trends and interactions between treatment effects and time. These analyses will utilize mixed-effects models with random intercepts for participants and fixed effects for time, considering autoregressive structures for residual errors.

To handle missing values, we will employ multiple imputation techniques under the assumption of missing at random (MAR). Given the potential for early dropout due to poor outcomes, we will also explore models that account for missing not at random (MNAR) based on informative dropout assumptions. As part of our sensitivity analyses for missing data, we will consider Bayesian models that can incorporate prior assumptions about the non-ignorable missing data mechanisms.

All statistical tests will be two-tailed, with a significance level set at *p* < 0.05. We will conduct both individual time-point analyses and longitudinal analyses to provide a comprehensive understanding of the treatment effects over time.

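### The planned treatment-by-time analysis counts baseline as an outcome visit, so a significant interaction is not evidence that the effect changes between weeks 12 and 48

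*Protocol article*

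**What the plan says.** The Analysis section makes change from baseline to week 12 in the three WOMAC subscales primary. It then adds a secondary "longitudinal analysis across all four time points to identify potential time trends and interactions between treatment effects and time", fitted with "mixed-effects models with random intercepts for participants and fixed effects for time, considering autoregressive structures for residual errors". It does not say whether time is categorical or linear.

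The Study design overview identifies the four time points: a baseline measurement, one straight after the 12-week programme, then two more "at 24 and 48 weeks to assess the durability of treatment effects". Table 1 lists the same four columns, so baseline is one of the outcome levels in this model.

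Other planned analyses bear on the later visits:

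- Analysis section, with the primary outcome as the model to follow: "Changes in knee pain at weeks 24 and 48, along with all other outcomes, are considered secondary and will be analyzed in the same manner".
- Analysis section: "We will conduct both individual time-point analyses and longitudinal analyses".
- Statistical analysis section: a repeated measures ANOVA in which, after a significant Group × Time interaction, "simple main effects will be analyzed to determine differences between specific groups at each time point", with Bonferroni adjustment.

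No section names an interaction restricted to the visits after baseline, or a contrast of the week-48 effect with the week-12 effect.

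**The concern.** Durability is a headline aim. The abstract's Discussion says "this trial is designed to determine whether these interventions offer durable clinical benefits", and the later visits exist for that purpose. The natural question for a treatment-by-time analysis is then whether the effect seen at week 12 holds, grows or fades by week 48.

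With baseline as an outcome level, the interaction test answers a different question. The arms are expected to be equal before treatment, so the interaction is null only if there is no effect at any later visit. A benefit that appears by week 12 and stays exactly the same to week 48 violates that null, and so does one that has vanished by week 48. A significant result could be read as an effect that varies over follow-up when it has been fully maintained, and the same result would arise if it had been lost.

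**Working it through.** **Inputs.** From the Sample size section: 40 per arm, 15% dropout (40 × 0.85 = 34 completers), mean difference 5.0, SD 9.0, f = 0.32, 80% power. Alpha is 0.05, two-sided. The within-person correlation is not given. I assume compound symmetry (CS) 0.3 to 0.7, AR(1) 0.5 to 0.7 per visit, and a random intercept carrying half the variance plus AR(1) 0.5.

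**The plan's own figure.** For a three-group ANCOVA with one covariate, λ = f² × N with 2 and N − 4 df. Power is 0.799 at N = 97 and 0.804 at N = 98. Rounding to equal arms gives 99, and 99 / 0.85 = 116.5, so 117. The stated 120 is within 3% of that. The plan gives no figure for the interaction test.

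**Effect profiles.** Both exercise arms differ from control by the following, at baseline / 12 / 24 / 48 weeks:

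- constant: 0 / 5 / 5 / 5
- fade to zero: 0 / 5 / 2.5 / 0
- abrupt loss: 0 / 5 / 0 / 0
- half lost: 0 / 5 / 3.75 / 2.5

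**Formula.** With n per arm, λ = n × (2/3) × (Cδ)′(CΣC′)⁻¹(Cδ). Here δ is the profile, C takes differences between visits, Σ is the covariance matrix, and 2/3 is the spread of the arm weights 1, 1, 0. Under CS this reduces to λ = n × (2/3) × SS / [σ²(1 − ρ)], where SS is the sum of squares of the profile about its own mean.

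**Worked case: CS 0.5, n = 34, σ²(1 − ρ) = 81 × 0.5 = 40.5**

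Four visits, 6 and 297 df:

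- constant: SS = 18.75, λ = 34 × (2/3) × 18.75 / 40.5 = 10.49, power 0.66
- abrupt loss: SS = 18.75, the same λ, power 0.66
- fade to zero: SS = 17.19, λ = 9.62, power 0.61

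Weeks 12, 24 and 48 only, 4 and 198 df:

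- constant: SS = 0, power 0.05
- fade to zero: SS = 12.5, λ = 7.00, power 0.53
- abrupt loss: SS = 16.67, λ = 9.33, power 0.67
- half lost: SS = 3.125, λ = 1.75, power 0.15

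**Across the assumed correlations, n = 34**

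| Correlation | Four-visit: constant | Four-visit: fade | Post-baseline: constant | Post-baseline: fade | Post-baseline: half lost |
|---|---|---|---|---|---|
| CS 0.3 | 0.49 | 0.45 | 0.05 | 0.39 | 0.12 |
| CS 0.5 | 0.66 | 0.61 | 0.05 | 0.53 | 0.15 |
| CS 0.7 | 0.89 | 0.86 | 0.05 | 0.78 | 0.23 |
| AR(1) 0.5 | 0.51 | 0.58 | 0.05 | 0.36 | 0.11 |
| AR(1) 0.7 | 0.73 | 0.85 | 0.05 | 0.52 | 0.15 |
| Intercept + AR(1) 0.5 | 0.85 | 0.91 | 0.05 | 0.67 | 0.19 |

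These post-baseline rates take no credit for a baseline covariate.

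**If time is linear in weeks.** The visit weeks 0, 12, 24 and 48 have mean 21 and centred sum of squares 1260. The constant profile has fitted slope 5 × (−9 + 3 + 27) / 1260 = 0.083 per week. The fade has (5 × (−9) + 2.5 × 3) / 1260 = −0.030. With CS 0.5 the test is significant in 0.49 of trials for the constant effect and 0.10 for the fade, so the maintained effect is flagged more often.

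**The planned week-48 comparison.** For change from baseline with correlation 0.5, the variance is 2 × 81 × 0.5 = 81 and λ = 34 × (2/3) × 25 / 81 = 7.00 with 2 and 99 df. Power is 0.64 if the effect is constant and 0.05 if it has gone by week 48.

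**The case against.** The strongest reply is that durability is examined elsewhere in the plan. The week-24 and week-48 analyses and the visit-by-visit comparisons ask whether benefit is present at each later visit, and the week-48 comparison separates a constant effect from a lost one well (0.64 against 0.05). This stands. A reader might infer that the trial cannot address durability at all, and the documents do not support that. What those comparisons leave out is the size of the change since week 12. Reading fading from a significant week-12 result and a non-significant week-48 result would compare p-values, not effects. The repeated measures ANOVA has the same property as the mixed model if baseline is one of its time levels.

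Second, a mixed model with categorical time already contains the right contrast, and an article may leave contrasts to a fuller plan. The first half is true, so the model need not be discarded. But the article itself says that the interaction is sought across all four time points. That is a stated choice, not an omission.

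Third, no section states a null hypothesis for this analysis, or says that a significant interaction will be reported as fading. That is also true. The misreading is a risk of the method, not something the protocol announces.

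Fourth, a reader might take the 49-89% as type I error inflation. It is not. With no effect at any visit the test keeps its 5% level, and these rates are power against a null other than the one of interest. Nor are the rates for constant and fading effects always close. Under AR(1) the fade is flagged 7 to 12 percentage points more often, abrupt loss 19 to 21 points more often, and with linear time the rates diverge widely.

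**Conclusion.** The point holds for the interaction test in the secondary longitudinal analysis, and only for that. With baseline as one of the four outcome visits, a significant group-by-time interaction is not evidence that the effect changes during follow-up. That follows from the expected baseline difference being zero and needs no assumption about correlation.

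The size does rest on assumptions: categorical time, 34 per arm, a 5-point effect in both exercise arms, SD 9 and the correlations listed. On these, the four-visit test is significant in about 49-89% of trials under a constant effect and 45-91% under a fade to zero. The post-baseline interaction gives 5% and about 36-78%. Linear time changes the rates but does not make the four-visit test suitable, because it then flags the constant effect more often.

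The week-12 primary comparison is untouched, and presence of benefit at weeks 24 and 48 is covered by other planned analyses. The remaining gap is that nothing planned estimates or tests the change in effect from week 12 to week 48. It is worth closing because durability is a stated aim.

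**What to change.** In the Analysis section, restate the longitudinal model in one of two ways:

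1. Make weeks 12, 24 and 48 the outcomes, with baseline score as covariate (and baseline-by-visit), group, categorical visit and group-by-visit. Keep the planned participant random intercept and autoregressive residuals.
2. Keep baseline as an outcome, constrain its mean to be equal across arms, and test only the post-baseline contrasts.

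In either case, base the durability statement on two estimates for each exercise arm against control, each with a 95% confidence interval: the difference at week 48, and the change in that difference from week 12 to week 48. Do not base it on the significance of the four-visit interaction.

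The cost is analysis wording. It needs no new data, visits or participants, and the Study status and timeline section says that recruitment had not begun at submission. The downside is modest power for partial fading: about 11-23% with 34 per arm when half the effect is lost by week 48. Durability should therefore be reported as an estimate with its interval, and a non-significant post-baseline interaction should not be taken as proof that the effect was maintained.

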### Cost-effectiveness analysis

Our study will conduct an economic evaluation to assess the cost-effectiveness of Tai Chi, Baduanjin, and health education for knee osteoarthritis management. We will focus on direct medical costs like intervention expenses, medications, and hospital stays, as well as indirect costs such as productivity losses. Quality-adjusted life years (QALYs) will be calculated using SF-36 utility scores to measure health state utilities. The cost per QALY gained will be the primary economic outcome, analyzed over the trial duration and in a projected extension.

To estimate long-term health and economic implications, we will use computer simulation models, including decision analysis to evaluate outcomes under uncertainty. This process will involve a literature review for model parameters and the development of Markov and Monte Carlo simulation models based on trial data. The cost-effectiveness analysis will present incremental cost-utility ratios, allowing comparison with accepted healthcare decision-making thresholds. Sensitivity analyses will be conducted to assess the impact of key parameter variations on the interventions' cost-effectiveness, ensuring a robust economic evaluation.

## Discussion

Our study introduces a randomized controlled trial featuring a distinctive three-arm design to assess the clinical efficacy of Tai Chi, Baduanjin, and health education for individuals with knee osteoarthritis. This approach allows for a direct comparison among these interventions, providing a clearer understanding of their relative benefits and potential as alternatives or complements to conventional treatments.

The inclusion of both traditional exercises and health education within the trial framework ensures a thorough evaluation of non-pharmacological strategies for knee osteoarthritis. By directly comparing Tai Chi and Baduanjin, our study aims to ascertain whether one intervention is superior or if they offer similar benefits, which is essential information for both patients and healthcare providers.

The results of this study are anticipated to enrich the evidence base for managing knee osteoarthritis through non-pharmacological means. The comprehensive clinical evaluation of these interventions is expected to yield valuable insights into their practical utility and effectiveness in improving patients' quality of life. This study's findings could support more informed decision-making in clinical practice, potentially influencing treatment guidelines and patient management strategies for knee osteoarthritis.

A primary limitation of this study is the imbalance in intervention frequency and contact time between the exercise groups (5 sessions/week) and the health education control group (1 session/week). This design reflects clinical guidelines recommending frequent practice for mind-body exercises, whereas the control represents standard care. Consequently, observed differences may be attributed to the comprehensive intervention package (including increased clinician attention and time commitment) rather than the specific physiological effects of Tai Chi or Baduanjin alone. Future studies employing dose-matched active controls are needed to isolate the specific modality effects.

Furthermore, as is inherent to behavioral interventions, participants and instructors could not be blinded, introducing potential performance bias. To mitigate this threat to internal validity, we strictly maintained blinded outcome assessment throughout the 48-week follow-up and incorporated objective physical performance measures to complement self-reported data.

While intervention fidelity is rigorously maintained during the initial 12-week supervised phase through standardized protocols and trained instructors, the subsequent unsupervised follow-up period relies partially on participant self-report (e.g., exercise logs). This shift may introduce variability in intervention exposure. We have implemented periodic telephone checks and log reviews to monitor adherence, but the potential for fidelity decay in the long term remains a limitation common to pragmatic trials.

Finally, the external validity of our findings may be constrained by the single-center setting within a specific Chinese hospital and the high frequency of required exercise sessions. These factors may limit the generalizability of results to healthcare systems with different resources or to community-dwelling older adults who may struggle with high-frequency adherence. Our findings should thus be interpreted as the efficacy of these interventions under optimal, supervised conditions. Future research should focus on adapting these protocols for diverse cultural contexts and evaluating their effectiveness in real-world, lower-resource community settings.

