### Tai Chi intervention

Participants assigned to the Tai Chi group will engage in a structured training program led by experienced instructors with over five years of teaching experience. The intervention will be based on a standardized “Simplified Tai Chi” protocol, specifically adapted for individuals with knee osteoarthritis. Over the course of 12 weeks, participants will attend five 60 min sessions per week, focusing on ten selected movements designed to improve balance, flexibility, and overall physical function without excessive joint stress. These movements include the Preparatory Stance, Rolling Back, Grasping the Knee and Twisting Step, Parting the Wild Horse's Mane, Cloud Hands, Golden Rooster Stands on One Leg, Toe Kick, Embracing the Sparrow's Tail, Cross Hands, and Closing Stance (32–34). Each session will begin with a 10 min warm-up, followed by practice of the Tai Chi movements, breathing techniques, and a 10 min cool-down period with relaxation methods. In addition to the supervised sessions, participants will also attend a weekly health education lecture for 12 weeks to further support their understanding of knee osteoarthritis management.

To ensure the quality and consistency of the intervention, all Tai Chi instructors will follow a standardized teaching protocol and receive training on the specific needs of individuals with knee osteoarthritis. Participants will be encouraged to practice Tai Chi at home for at least 20 min per day, with weekly assignments provided by the instructors to reinforce learning. Adherence to the home practice will be monitored through weekly feedback forms, and the quality of the sessions will be regularly assessed through video recordings and instructor feedback. After completing the 12-week intervention, participants will be asked to continue practicing Tai Chi independently, with monthly follow-up calls from the research team to monitor adherence and provide support as needed. Follow-up assessments will be conducted at Weeks 24 and 48 to evaluate the long-term effects of the Tai Chi intervention on pain, stiffness, physical function, and quality of life.

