### Baduanjin intervention

Participants in the Baduanjin group will be led by experienced instructors through a 12-week program focusing on ten specific movements of the Baduanjin exercise routine. This traditional Chinese practice, known as “Health Qigong … Baduanjin”, is standardized by the General Administration of Sport of China. The series includes the following movements: Preparatory Posture, Holding Up the Three Burns with Both Hands, Left-Right Bow and Arrow Stance, Regulating the Stomach and Spleen by Raising Hands, Seven Injuries and Laboring to Look Back, Weaving Fingers to Strengthen the Waist, Clenching Fists and Angry Gaze to Enhance Energy, and Seven Injuries and Laboring to Look Back (35–37). Each session will start with a 10 min warm-up, followed by 40 min of Baduanjin practice, and conclude with a 10 min cool-down period to ensure proper form and technique are maintained throughout the exercise.

To maintain the quality and consistency of the Baduanjin intervention, instructors will follow a standardized protocol and provide weekly assignments to reinforce home practice. Participants will practice Baduanjin daily for at least 20 min, with adherence monitored through weekly feedback. Video recordings and instructor feedback will regularly assess session quality. Both the Tai Chi and Baduanjin groups will attend weekly health education lectures. After the 12-week intervention, participants will continue practicing independently, with monthly follow-ups from the research team. Follow-up assessments at Weeks 24 and 48 will evaluate the long-term effects on pain, stiffness, physical function, and quality of life.

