### Health education intervention

The Health Education intervention, designated as the control group, will focus on providing participants with essential knowledge about knee osteoarthritis and general health management. Unlike the Tai Chi and Baduanjin groups, this group will not receive any standardized exercise regimen but will instead participate in weekly health education lectures. These sessions, each lasting 60 min with a 45 min presentation followed by a 15 min discussion, will cover a range of health-related topics. To ensure content standardization, the curriculum is divided into three core modules: (1) OA Management (pathophysiology and self-care); (2) Lifestyle & Exercise Science (principles of resistance, aerobic, and flexibility training, and obesity management); and (3) Comorbidity Prevention (management of diabetes, hypertension, and seasonal dietary practices).

The goal of this intervention is to ensure that all participants, regardless of their assigned group, receive a baseline level of health education, which can help them make informed decisions about their health and lifestyle. This approach allows for a balanced comparison of the additional benefits of the standardized exercise programs in the Tai Chi and Baduanjin groups.

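### The trial aims to say whether Tai Chi and Baduanjin give similar benefit and whether they work as standalone therapies, but difference tests with lectures in every arm support neither statement

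*Protocol article*

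**What the plan says.** On the two exercises, the Discussion states that "our study aims to ascertain whether one intervention is superior or if they offer similar benefits". The Discussion part of the Abstract states that "this trial is designed to determine whether these interventions offer durable clinical benefits as standalone therapies or provide additive value".

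The inferential tools are in two sections. Statistical analysis says: "For comparisons among the three groups, one-way Analysis of Variance (ANOVA) will be used". Bonferroni pairwise comparisons follow only if that test is significant. For the primary outcome, a repeated-measures ANOVA leads to group comparisons at each time point only if the group-by-time interaction is significant. The Analysis section makes all tests two-tailed at 0.05. The Sample size section targets a between-group difference: f = 0.32, described as about 5.0 points with a common SD of 9.0, 80% power and 15% dropout, giving 120 participants, 40 per arm. Neither an equivalence or non-inferiority hypothesis, nor a margin, nor an interval rule for similarity appears.

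On the content of the arms, the Tai Chi section says "participants will also attend a weekly health education lecture for 12 weeks", and the Baduanjin section says "Both the Tai Chi and Baduanjin groups will attend weekly health education lectures". Of the control, the Health education section says "this group will not receive any standardized exercise regimen but will instead participate in weekly health education lectures". The same section gives the purpose of the common lectures: "This approach allows for a balanced comparison of the additional benefits of the standardized exercise programs". The Abstract's methods and the Study design overview list only the exercise sessions for the two exercise arms.

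**The concern.** A stated aim should be answerable by the planned analysis. Two are not.

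First, similarity. A test of difference has two outcomes: a difference is shown, or it is not. The second does not establish that two treatments are alike, least of all when the interval is about as wide as the difference the trial was built to detect. Under the gating rule, Tai Chi and Baduanjin may not be compared directly at all if the overall test fails, which is one of the situations in which a reader would most want the estimate.

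Second, standalone benefit. If exercise plus lectures is compared with lectures, the estimable quantity is what exercise adds to lectures. The effect of exercise given alone is not observed in any arm.

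The Discussion expects the results to inform clinical decisions and possibly guidelines. A statement that the exercises are interchangeable, or that either suffices alone, would go beyond what the trial can show.

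**Working it through.** **Reproducing the plan's figure.** Three groups, f = 0.32, alpha 0.05, noncentral F with noncentrality N × f² and one covariate: 80% power is first reached at N = 98, or 99 for equal arms. Allowing for dropout, 99 / 0.85 = 117, close to the stated 120. In reverse, 40 × 0.85 = 34 per arm, 102 in all, with power 0.82. The planned size is therefore explained by an overall test of difference.

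**Inputs for Tai Chi minus Baduanjin.** SD 9.0 and design difference 5.0 (Sample size section). Evaluable number: 34 per arm after 15% dropout, or 40 if missing week-12 values are imputed as no change, as the Analysis section plans for the primary analysis.

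**Precision.** SE = 9 × √(2/n), which is 2.183 at n = 34 and 2.012 at n = 40. Half-width = t × SE, with variance pooled over three arms (99 or 117 df).

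| n per arm | 95% half-width | Bonferroni (three pairs) half-width |
|---|---|---|
| 34 | 1.984 × 2.183 = 4.33 | 2.435 × 2.183 = 5.32 |
| 40 | 1.980 × 2.012 = 3.99 | 2.429 × 2.012 = 4.89 |

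**Power to detect a true 5.0-point difference.** Noncentral t with noncentrality 5/SE (2.29 at n = 34, 2.48 at n = 40): about 62% and 69% unadjusted; about 44 to 45% and 52% with Bonferroni (the lower figure at n = 34 uses the two arms' own 66 df). A non-significant result would thus arise in 31 to 38% of trials unadjusted, and in about half with Bonferroni, even if the exercises truly differed by the whole design difference.

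**Could similarity be shown at this size?** The documents give no margin, so the margins here are assumptions. For two one-sided tests at 0.05 and a true difference of zero, power ≈ 2Φ(margin/SE − t) − 1, with t = 1.660 (n = 34) or 1.658 (n = 40).

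| Assumed margin | n = 34 | n = 40 | n per arm for 80% power (after 15% dropout) |
|---|---|---|---|
| 5 points | 2Φ(0.63) − 1 = 47% | 2Φ(0.83) − 1 = 59% | 56 (66) |
| 4 points | 2Φ(0.17) − 1 = 14% | 2Φ(0.33) − 1 = 26% | 87 (103) |
| 3 points | about 0 | about 0 | 155 (183) |

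The last column is 2 × [9 × (1.645 + 1.282)/margin]², rounded up, then divided by 0.85. At 3 points the power is about nil because the 90% half-width (3.62 or 3.34) exceeds the margin. If a 95% interval must lie inside the margin, power at 5 points is about 26 to 40% (normal approximation).

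**Standalone benefit.** No arithmetic applies. The arms set side by side are:
- Tai Chi arm: Tai Chi plus lectures
- Baduanjin arm: Baduanjin plus lectures
- Control arm: lectures

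Each contrast with control estimates exercise added to lectures. The additive half of the Abstract's sentence is answerable; the standalone half is not.

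**The case against.** The similarity wording is one sentence in the Discussion and speaks of ascertaining whether, not of proving. The Background's aims concern comparative effectiveness and advantage over health education, which superiority tests serve, and an analysis plan that is not shown could add a margin. All this is fair. A reader might infer that the investigators promise equivalence, or have decided to read a non-significant test as similarity; the document says neither. What stands is that an aim is stated with no route to it, and that a later margin would not rescue it at this size unless it were wider than the design difference.

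A reader might also infer that even an observed difference of exactly zero could not exclude 5.0 points. That holds only for the Bonferroni interval at 34 per arm (5.32). At 40 per arm, the number in the primary analysis under the no-change imputation, that interval is 4.89, and the unadjusted 95% interval excludes 5.0 at either size. The plan does not support this stronger claim. Nor does it assign the 5.0 points to Tai Chi versus Baduanjin or offer them as a margin; they serve here only as a yardstick.

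On the second half, the Health education section already describes an add-on contrast, and the limitations concede that differences may reflect the whole package and unequal contact time. Standalone might also mean without conventional treatment: the Discussion mentions alternatives or complements to such treatment, and recent drug or physical therapy for knee osteoarthritis is an exclusion. The wording is therefore ambiguous rather than plainly impossible. But that exclusion covers only the month before entry, medication use is a possible covariate in secondary analyses, and no arm or contrast addresses exercise without conventional treatment. Neither reading makes the standalone claim testable.

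**Conclusion.** The point holds in a limited form. The stated aim of finding similar benefits has no matching analysis. The Tai Chi versus Baduanjin interval would be about ±4.0 to 4.3 points (±4.9 to 5.3 with Bonferroni) beside a design difference of 5.0, and a non-significant result would be uninformative about similarity. The standalone claim in the Abstract is not estimable from the arms described, while the added benefit over lectures is.

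The figures rest on SD 9.0 for the analysed change score, a common variance and 34 to 40 per arm. Imputing no change could alter the SD and the difference, and baseline adjustment could narrow the interval. The equivalence figures also rest on assumed margins and a true difference of zero. The tests against control are not put in doubt by this point; what is affected is what the trial may conclude.

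**What to change.** 1. Report the Tai Chi minus Baduanjin estimate with its confidence interval whatever the overall test or interaction shows.
2. Before recruitment, either state a justified margin, the interval level and the rule that similarity is claimed only if the interval lies wholly inside the margin (otherwise: no difference shown), together with the power this has at 120 participants; or remove the similarity aim from the Discussion if no margin can be justified at this size.
3. In the Abstract's Discussion, replace the standalone-or-additive clause by: benefit when added to weekly health education.
4. In the Abstract's methods and the Study design overview, describe the exercise arms as exercise plus weekly lectures.

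The cost is a few sentences and somewhat narrower claims. The Study status section says recruitment had not begun at submission, so nothing already collected is affected. Only a decision to power the trial for similarity would cost participants: about 66 per arm randomised for an assumed 5-point margin, 103 for 4 points and 183 for 3 points, against the planned 40.
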